## Abstract

**Background:**

The pain management of postherpetic neuralgia (PHN) remains a major challenge, with no immediate relief. Nitrous oxide/oxygen mixture has the advantages of quick analgesic effect and well-tolerated. The purpose of this study is to investigate the analgesic effect and safety of nitrous oxide/oxygen mixture in patients with PHN.

**Methods/design:**

This study is a single-center, two-group (1:1), randomized, placebo-controlled, double-blind clinical trial. A total of 42 patients with postherpetic neuralgia will be recruited and randomly divided into the intervention group and the control group. The control group will receive routine treatment plus oxygen, and the intervention group will receive routine treatment plus nitrous oxide/oxygen mixture. Data collectors, patients, and clinicians are all blind to the therapy. The outcomes of each group will be monitored at baseline (T0), 5 min (T1), and 15 min (T2) after the start of the therapy and at 5 min after the end of the therapy (T3). The primary outcome measure will be the pain intensity. Secondary outcomes included physiological parameters, adverse effects, patients’ acceptance of analgesia, and satisfaction from patients.

**Discussion:**

Previous studies have shown that nitrous oxide/oxygen mixture can effectively relieve cancer patients with breakthrough pain. This study will explore the analgesic effect of oxide/oxygen mixture on PHN. If beneficial to patients with PHN, it will contribute to the pain management of PHN.

**Trial registration:**

Chinese Clinical Trial Register ChiCTR1900023730. Registered on 9 June 2019

**Supplementary Information:**

The online version contains supplementary material available at 10.1186/s13063-020-04960-5.

## Background

Postherpetic neuralgia (PHN) is a major complication of herpes zoster (HZ), and the definition of PHN is arbitrary but involves pain that lasts for 90 days or more from the onset of the HZ [1]. PHN is more common; one study found that the overall incidence of PHN was 3.9–42.0/100,000 person-years [2]. Age is a major risk factor for PHN, with a 4% risk of developing PHN under age 50 and a 34% risk over age 80 [3]. The proportion of the world’s population over 60 is expected to double in the next 50 years [4]. With the rapid increase in life expectancy, the incidence of PHN may rise sharply [5].

Spontaneous pain is common in PHN and can be intermittent or persistent. Pain has a variety of qualities, such as burning, throbbing, aching, stabbing pain, or electric-shock-like pain. Besides, allodynia and hyperalgesia have also been reported [6, 7]. PHN seriously harms the physical, psychological, and daily activities of patients. Patients lack appetite, lose weight, have trouble sleeping, and are reluctant to communicate with others. Some even suffer from depression and anxiety [8]. PHN also has a serious negative impact on an individual’s work; one study found that 64% of 88 participants missed work and 76% were less productive on account of HZ and PHN [9].

As mentioned above, PHN not only is physical pain but also causes irreparable detriment to all aspects of the patients. Effective treatment for PHN is urgently needed. However, there is no cure for PHN, and the main goal of current treatment is pain relief [10, 11]. The Neuropathic Pain Special Interest Group of the International Association for the Study of Pain (NeuPSIG) proposed some suggestions for the treatment of PHN. They advised gabapentin, pregabalin, and tricyclic antidepressants (TCAs) as first-line therapy; 5% lidocaine as second-line treatment; and opioids as third-line treatment [12]. But even with the most effective drugs, less than 50% of patients experience significant reduction (> 50%) in pain [13]. Gabapentin and pregabalin analgesia work slowly and take weeks to titrate to the therapeutic dose [14, 15]. Patients receiving the lowest dose of gabapentin continued treatment for an average of 17 weeks. The average daily dose of pregabalin is 187 mg, the average maximum dose is 222 mg, and it takes an average of 30 days to reach the maximum dose [14]. TCAs show a relatively slow onset of action with potentially troublesome adverse effects, such as cognitive impairment, excessive sedation, and cardiotoxicity (myocardial ischemia and arrhythmia) [16–18]. Five percent lidocaine takes hours (≤ 4 h) to act as an analgesic, acting faster than gabapentin or pregabalin [19]. These drugs are the most commonly used drugs to relieve PHN pain in clinical practice, which require a relatively long treatment period and cannot quickly relieve patients’ severe acute pain. Strong opioids such as oxycodone and morphine are comparable to TCAs in reducing pain in PHN patients and can quickly relieve severe acute pain [20]. Presumably for these reasons, one study found that 21.6% of PHN patients frequently used opioids as first-line therapy [21]. But the current guidelines for treating PHN with opioids are controversial [16]. This is not only related to the side effects of opioids such as constipation, nausea, and sedation, but PHN patients treated with opioids also have a higher medical burden [21, 22]. Besides, any physician who prescribes opioids should assess each patient’s personal and family history of substance abuse. And prescribing people must commit to regular monitoring of patients’ urine drug tests and stop taking opioids if there are signs of abuse [22]. That is, not all patients with PHN can use opioids for pain relief. Therefore, there is an urgent need to find a treatment that can relieve severe acute pain in PHN patients instead of opioids.

Nitrous oxide/oxygen mixture has been shown to have a fast and safe analgesic effect. In 1799, Humphrey discovered that nitrous oxide had anesthetic and analgesic effects [23]. The nitrous oxide does not irritate the respiratory tract, has very low solubility in the blood, and does not bind to the protein [24]. Nitrous oxide plays an analgesic role by stimulating the beta endorphin system and antagonizing the *N*-methyl-d-aspartic acid receptor [25]. Studies have shown that 30% of nitrous oxide produces an analgesic effect equivalent to 10–15 mg of morphine [26, 27]. In clinical practice, nitrous oxide and oxygen are mixed in different proportions for anesthesia or analgesia [28]. The nitrous oxide/oxygen mixture is stored in a pre-mixed cylinder and can be inhaled through a facemask or nasal catheter for self-administered analgesic. When inhaling nitrous oxide/oxygen mixture for analgesia, the patient is conscious, and adverse reactions are uncommon [29]. Now, it has been used in many countries around the world to relieve a wide variety of pain, such as childbirth [30], dental procedures [31], burn dressing [32], cancer patients with breakthrough pain [33], lumbar punctures [34], and other painful conditions. Another advantage of nitrous oxide/oxygen mixture is that it works quickly and recovers quickly [35]. Also, nitrous oxide/oxygen mixture is easily controlled and does not require a professional anesthesiologist to operate [36]. Side effects were mild and quickly resolved after cessation of inhalation [29]. Taking these advantages into account, this study will be conducted to explore the analgesic efficacy and safety of a fixed nitrous oxide/oxygen mixture (Patent no. ZL 2013 1 0053336.X) on PHN through a randomized controlled trial.

This study hypothesizes that the inhalation of nitrous oxide/oxygen mixture will be able to relieve pain in patients with PHN. It will be possible to replace opioids if nitrous oxide/oxygen mixture can effectively and rapidly relieve pain in patients with PHN, thereby reducing the risk of opioid abuse and lightening the financial burden on patients.

## Methods/design

### Aim

The main aim of the study is to evaluate the analgesic effect of the fixed nitrous oxide/oxygen mixture on patients with PHN. There are three secondary aims of the study:
To evaluate the safety of the fixed nitrous oxide/oxygen mixture by monitoring patients’ physiological parameters and adverse effectsTo determine the satisfaction of patients with the analgesic effect of the fixed nitrous oxide/oxygen mixtureTo investigate the acceptance of patients to the fixed nitrous oxide/oxygen mixture analgesia

### Study design

This study is a single-center, two-group (1:1), randomized, placebo-controlled, double-blind clinical efficacy trial. We intend to investigate the analgesic effect and safety of nitrous oxide/oxygen mixture for PHN patients. Eligible participants will be randomly assigned to either the intervention group (nitrous oxide/oxygen mixture) or the control group (oxygen) based on computer-generated random numbers. The whole study design is shown in Fig. 1.

**Fig. 1 Fig1:**
[figure not shown]
Study design framework. PHN postherpetic neuralgia, NRS numerical rating scale, SpO2 percutaneous oxygen saturation, HR heart rate, BP blood pressure, RTO routine treatment plus oxygen, RTN routine treatment plus nitrous oxide/oxygen mixture

The protocol was approved by the Ethics Committee of the General Hospital of Ningxia Medical University (Reference No: 2018-373). The trial was registered with the Chinese Clinical Trial Registry (ChiCTR1900023730) on 9 June 2019. We adhered to Standard Protocol Items Recommendations for Interventional Trials (SPIRIT) for the design of the test (see Additional file 1).

### Study setting

This study will be conducted in the pain department of the General Hospital of Ningxia Medical University. This hospital is a tertiary hospital with functions of medical treatment, teaching, and scientific research. Approximately 100 PHN inpatients are admitted to the pain unit each year. This is sufficient to meet the sample size requirement.

### Study participants

All patients with postherpetic neuralgia admitted to the pain unit will be invited to participate in this study.

#### Inclusion criteria

Patients who meet the following inclusion criteria will be enrolled in the trial:
The patient met the Chinese PHN clinical diagnostic criteria (PHN is defined as pain persisting for ≥ 1 month after HZ rash healing [37]);Over the age of 18;Pain score ≥ 4 according to the Numerical Rating Scale (NRS); andVolunteered to participate and signed the informed consent.

#### Exclusion criteria

Patients who have one of the following conditions are not allowed to participate in the trial:
Women who are pregnant;The patient diagnosed with intestinal obstruction, air embolism, pneumothorax, and obstructive respiratory disease;The patient’s clinical history includes epilepsy;The patient suffers from otorhinolaryngologic diseases, such as sinusitis, middle ear disease, and eardrum transplantation;Patient who is unable to report pain; andCritically ill patients: (1) patients in intensive care, (2) patients after surgery, (3) patients with severe trauma or extensive burns, (4) patients with ventilator-assisted breathing, and (5) patients with life-threatening conditions requiring monitoring of vital signs.

### Recruitment

This study will be conducted in the pain department of the General Hospital of Ningxia Medical University. The number of PHN patients admitted to the pain department each year is enough to meet the sample size of this study. We will recruit participants through the pain department’s WeChat public platform, posters, and medical staff introductions. For patients who wish to participate in the study, researchers will elaborate on the purpose, methods, possible risks, and rights of participants. If the patient is fully aware of the study and agrees to participate and meets the inclusion criteria, the investigator will have the patient sign the informed consent.

### Randomization, allocation concealment, and blinding

Patients who meet the inclusion criteria will be randomly assigned to the intervention group and control group at a 1:1 allocation ratio after recruitment. The randomly assigned list will be computer-generated and performed by a statistician who is not involved in the trial and will be stored in a sealed, opaque envelope kept by the project manager. To ensure that the trial is double-blind, no investigator or patient will know about the randomization, only the project manager responsible for the gas distribution. The nitrous oxide/oxygen mixture and the oxygen will be supplied by the Ningfeng Oxygen Company, and the cylinder packaging of the two gases is identical. The letters A and B will be used to identify the two gases, and only the project manager will know what type of gas each letter represents. The project manager will distribute the gas according to the randomly assigned list.

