### Interventions

A clinician is responsible for assessing the patient’s condition on the ward, determining whether the patient meets the inclusion criteria, and informing the patient of the purpose of the trial, methods, possible risks, and rights of participants. Patients who meet the inclusion criteria will sign an informed consent form after agreeing to participate in the trial. The project manager will group patients who agree to participate in the trial based on the randomly assigned list and escort the patient to the treatment room, where the trial will be conducted. All patients in the trial will receive routine treatment (oral pregabalin 75 mg twice daily). Patients in the intervention group will inhale nitrous oxide/oxygen mixture with a facemask, which is a visible intervention measure. To eliminate the influence of psychological factors on the experimental results of patients in the control group, patients in the control group will inhale oxygen by a facemask. Patients in the intervention group will receive routine treatment plus a fixed nitrous oxide/oxygen mixture (contains 65% nitrous oxide and 35% oxygen), while patients in the control group will receive routine treatment plus oxygen. Before inhaling the gas, the data collector will teach the patient to use the NRS to report pain intensity. Besides, the data collector will inform patients that they have the right to stop or quit the trial at any time if they experience discomfort during the study. Before the trial begins (T0), the data collector will record the patient’s demographic and baseline characteristics; assess the patient’s pain intensity; measure heart rate, blood pressure, and percutaneous oxygen saturation; and teach the patient to inhale gas using a facemask. Patients in both groups will inhale gas using an oral-nasal mask, which is disposable and has a one-way valve. According to our previous research, the gas intake will last for 15 min [33, 34]. When the data collector opens the valve of the cylinder and the patient puts on the mask to inhale the gas, the trial will start timing. The data collector will assess the patient’s pain intensity and measure blood pressure, heart rate, and percutaneous oxygen saturation at the beginning of the trial at 5 min (T1) and 15 min (T2). To assess the patient’s pain, the data collector will ask the patient: How bad is the pain now? Patients will point to the corresponding pain score with their fingers and without having to remove the facemask. Five minutes after the end of the trial (T3), in addition to collecting the data mentioned above, the data collector will ask patients about their satisfaction with pain relief and acceptance of analgesic methods. Throughout the trial, the data collector will closely observe and ask the patient whether there are adverse effects.

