
Nitrous oxide/oxygen mixture has been widely used for pain relief with mild adverse effects and quick recovery [29]. Adverse effects of nitrous oxide/oxygen mixture have been reported in the literature, including nausea, vomiting, dizziness, drowsiness, headache, hypotension, and oxygen desaturation [29]. These adverse reactions usually do not require medication and recover quickly [29]. If any adverse effects occur or the patient requests that the trial be discontinued, the data collector can determine whether the trial should continue. The reason for trial stopped will be recorded by the data collector. The project manager will accompany the patient to participate in the trial but does not involve in the collection of trial data. Only the project manager knows what kind of gas the patient is breathing. During the trial, the project manager will take treatment measures if the patient has adverse effects.

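### One fixed letter per gas for the whole trial lets a single correct guess by a data collector carry over to later patients

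*Protocol article*

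**What the plan says.** The Study design section describes a "single-center, two-group (1:1), randomized, placebo-controlled, double-blind clinical efficacy trial", and the abstract adds: "Data collectors, patients, and clinicians are all blind to the therapy".

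The section on randomization, allocation concealment and blinding sets up the coding: "The letters A and B will be used to identify the two gases". It leaves the key to those letters with a single person: "only the project manager will know what type of gas each letter represents". One safeguard appears in the same section: "the cylinder packaging of the two gases is identical".

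Under Interventions, the data collector handles the cylinder. Timing starts at this point: "When the data collector opens the valve of the cylinder and the patient puts on the mask". The same person asks for the pain score, measures blood pressure, heart rate and oxygen saturation, and observes the patient for adverse effects throughout. Both groups wear a mask, which the protocol explains as a control for psychological influence.

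The Interventions section also describes the one unblinded role: "The project manager will accompany the patient to participate in the trial but does not involve in the collection of trial data". On who knows the gas, it says: "Only the project manager knows what kind of gas the patient is breathing". That person also treats adverse effects during the session.

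The section on data collection keeps the data collectors the same throughout the trial and includes training in how to maintain the double blind. The primary outcome is the patient's own 0 to 10 pain rating, given by pointing.

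**The concern.** No coding scheme stops someone guessing an active gas from one patient's reaction. A coding scheme does decide what that guess is worth afterwards. With one letter per gas, a collector who works out a letter once has also classified later patients who show no reaction at all. Because the collectors do not change, what they learn accumulates.

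The outcomes at stake are subjective. The collector elicits the pain rating while the gas is being inhaled (T1 and T2) and again 5 minutes after it ends (T3), when satisfaction and acceptance are also asked. A collector who knows the gas may ask, wait or respond differently, and that difference would be counted as treatment effect. An unblinded project manager in the same session is a further possible source of cues.

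**Working it through.** The documents give no figure for blinding, so there is none to reproduce. The check takes the text first, then the structural exposure, then what assumed rates would imply.

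**1. The links in the chain**

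| Link | Where | Status |
|---|---|---|
| Two codes, one per gas | Randomization, allocation concealment, and blinding | Stated |
| Collector opens the cylinder valve | Interventions | Stated |
| Same collectors throughout | Data collection, management, and confidentiality | Stated |
| Collector observes reactions and asks for the score | Interventions | Stated |
| Active gas can cause noticeable effects (seven listed, including dizziness, drowsiness and oxygen desaturation) | Interventions; Measurement | Stated, without rates |
| Collector sees the letter | – | Inferred: letters distinguish otherwise identical cylinders, and the collector handles the cylinder |

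**2. Structural exposure**

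Planned total: 42 patients, 21 per group (Sample size calculation). If a letter is decoded after k patients have been treated, the number of later patients exposed to a collector who sees every letter is at most 42 − k.

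- k = 20, the number recruited at manuscript submission (Trial status): 42 − 20 = 22 later patients.
- Patient-specific codes: the cue exposes that one patient and none by carry-over.

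**3. How likely one identifying reaction is, under assumed rates**

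Let p be the proportion of active-gas patients whose reaction leads a collector to the correct gas. The documents do not give p. The values below are assumptions, and patients are taken as independent. The chance of at least one such patient among m active patients is 1 − (1 − p)^m.

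| Assumed p | First 10 active patients | All 21 active patients |
|---|---|---|
| 5% | 1 − 0.95^10 = 40% | 1 − 0.95^21 = 66% |
| 10% | 1 − 0.90^10 = 65% | 1 − 0.90^21 = 89% |
| 20% | 1 − 0.80^10 = 89% | 1 − 0.80^21 = 99% |
| 30% | 1 − 0.70^10 = 97% | 1 − 0.70^21 = 99.9% |

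**4. What a shift would do, under assumed shifts**

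Take no true effect, the protocol's SD of 1.93 and 21 per group. The standard error is 1.93 × √(2/21) = 0.596. For an average between-group shift b in the pain rating, the two-sided 5% rejection probability (normal approximation) is 1 − Φ(1.96 − b/0.596) + Φ(−1.96 − b/0.596).

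- b = 0.25: about 7%
- b = 0.5: about 13%
- b = 1.0: about 39%

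Here b is averaged over the whole trial. Scores recorded before decoding are unaffected, so the shift among later patients would have to be larger than b to produce it. Steps 3 and 4 show sensitivity only; they do not estimate this trial's bias.

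**The case against.** The strongest reply is that much of the chain is not demonstrated. The text does not say that the letter is printed on the cylinder or shown to the collector. The Background calls adverse reactions uncommon, and several listed effects are non-specific, so one event need not decode a letter. Patients point to their own score in answer to a set question, which limits a collector's influence. The protocol also states real safeguards: identical packaging, masks in both groups, training in blinding, and a project manager who does not collect data. Room and cylinder handling may be set out in the full protocol, which is not shown.

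These points limit the size of the concern and its certainty, and they stand to that extent. They do not remove the carry-over. Identical packaging and masks conceal the gas only until a letter is decoded, and nothing stated limits a correct guess to the patient who prompted it. The two-letter scheme is also something the article specifies, not a detail it leaves out.

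Stronger readings are tempting but are not supported:

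- *One decoded letter compromises all 42 patients, past and future.* Scores already recorded cannot be biased by later decoding. Only someone who sees the letters gains anything, and patients, with one described session, would have to learn the letter from someone else.
- *A few sessions are enough to decode it.* No adverse-effect rate supports this.
- *The unblinded project manager contradicts the statement that clinicians are blind.* The manager is a disclosed exception and is never called a clinician. Treating adverse effects while unblinded creates a tension with that statement, but not a proven contradiction.
- *The double-blind claim has failed.* The text shows a route by which it could fail, not that it has.

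**Conclusion.** The point holds as a design weakness with an inexpensive remedy. One fixed letter per gas, combined with fixed collectors who handle the cylinder and elicit a self-reported score, allows a single correct inference to reveal the gas of later patients. It rests on one inference, that collectors see the letter, and on at least one recognisable reaction or cue being read correctly. The bias cannot be computed from the documents. What can be stated is the structure: up to 42 − k later patients under A/B coding, against none by carry-over under patient-specific codes. The effect falls mainly on the staff who see the letters.

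**What to change.** For the patients still to be treated, replace A/B with a unique patient-specific code on each cylinder, with no pattern that tracks the group. There are two ways to do this:

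- the gas supplier applies the codes off-site from the list made by the off-trial statistician; or
- the project manager puts a coded cover label over the letter before the session.

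Either way, data collectors should never see a code shared between patients. Report the A/B coding as a limitation for patients already treated. The count of 20 recruited is from manuscript submission, so the number who can still benefit must be checked.

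The cost is somewhat more labelling and supply logistics. The total of 42, the endpoints and the tests are unchanged. Patient-specific codes do not stop guessing within a session; they stop the guess from carrying over. The cover-label option leaves knowledge of the gas where it is now. If the off-site option changes who knows the gas, that must be reconciled with the Interventions section, where the project manager accompanies the patient and treats adverse effects.
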